### Variables

#### Outcome measures

#### Process evaluation

1. The performance level of the small group collaborative.

2. Process data such as attendance at meetings, actually creating working agreements, following the LQIC strategy, the number of groups that complete participation, and the number of regions actually participating.

#### Effect evaluation

1. The volumes of particular tests ordered and particular drugs prescribed for which the group has agreed that change, either decrease or increase, would be necessary.

2. The total volumes of tests ordered and drugs prescribed by the participating GPs for the clinical topics chosen.

3. The inter-physician variation in test ordering and prescribing behaviour for the clinical topics chosen.

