The Dutch Institute for the Proper Use of Medicine (DGV) supports and initiates local or regional implementation of quality improvement projects on the use of drugs and supports local PTAM groups by supplying them with information and educational materials [28]. Performance levels of PTAM groups are assessed once a year and rated on the basis of four levels, level one being the poorest level of performance and level four the highest. We will use this division into levels as a parameter for pre-randomization stratification.

Participation in PTAM groups by GPs is facilitated by national and regional support organizations for primary care, as well as by the government and through incentives by insurance companies. Attendance at PTAM meetings is rewarded by accreditation. Currently, approximately 50% of the group meetings reach the desired level of performance described by policymakers [27]. To reach this level, groups must at least use feedback on prescribing, create working agreements, discuss barriers to change, and evaluate working agreements. Most groups are stable and remain together for 10 years or more, with members mostly being replaced gradually [27]. Because of the nature and stability of these groups, they provide an excellent and safe environment for participants to discuss their own behaviour and barriers to change. We expect this existing system of PTAM groups will ensure sustainability of the implementation itself. Therefore, we plan to use these groups in a large pragmatic trial on the implementation of guidelines, using the strategy previously tested by [name] *et al*. [7]. However, we will expand the strategy, using social interaction and external influencing as key approaches for establishing behavioural change, to both test ordering and drug prescribing. In our view, the groups will no longer function merely as a PTAM group, but rather begin acting as LQICs. This trial is expected to show whether the effects found in less pragmatic trials can be confirmed. Aiming at both test ordering and drug prescribing, our combination strategy could lead to an even larger effect because of synergy. We will also evaluate the costs of implementing the strategy on a large scale.

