### Sample size

A sample size calculation is not really possible beforehand, because it is not yet known what working agreements will be created and with respect to what tests or drugs. The specific targets, incorporated in working agreements will probably be based on extreme overuse or underuse of certain tests or drugs by some or all group members. It is possible, for instance, that the group will decide to eliminate a particular obsolete test or drug or create a working agreement to decrease or increase the mean volume of tests ordered or drugs prescribed by 20%, from 35% to 55%.

The sample size calculation used in this trial is as follows: to detect an improvement of 20% in a certain target between groups, assuming an ICC of 0.10 [5], an alpha of 0.05 and a beta of 0.1 and a mean group size of seven, 44 LQICs would be needed. Anticipating a dropout of 10%, we would need to recruit 50 groups. A population this large would account for approximately 900,000 registered patients.

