### Intervention

Several theories have been postulated on how change in healthcare can be accomplished, and how effective change strategies can work in implementation of innovation. In cognitive theories, professional behaviour is considered to result from rational processes and experiences from earlier caseloads. In social interaction theories, change of professional behaviour is thought to be strongly mediated by peers in a group, the strength of inter-individual ties within groups, the existence of opinion leaders, and how much the desired behaviour is consistent with, and fits in, everyday practice. In total quality management theories, the use of systematically gathered data is considered to be crucial to facilitate effective professional development. These data can then be used in plan-do-study-act cycles (PDSA cycles) to provide insight into displayed behaviour and help identify areas where improvement is possible. This leads to the description of targets. These theories may overlap or may be complementary. In implementation science, the use of these theories as a framework is considered obligatory [32]. This intervention therefore will be multifaceted and consist of audit, comparative graphical feedback, and small group work with peer review of each other's performance, discussion of barriers to change, reaching agreement on future policy, and testing the agreement. After randomization to arm A or B, each group can choose from the corresponding set of five clinical topics allocated to that arm, to decide which three topics they want to discuss. Two balanced sets of topics, one for each arm, have been defined by the researchers. Each set consists of three major topics, from which the group has to choose two, and two minor topics, one of which has to be chosen. Thus, each LQIC will be asked to complete the entire strategy for three clinical topics of their choice during the intervention period. They are free to schedule extra meetings on topics not included in this trial, but these meetings will not be included in the final analysis. Feedback on the topic under discussion will be sent to the medical coordinator (diagnostic feedback) or local community pharmacists (prescription feedback) two weeks prior to the test ordering or the prescribing session of the LQIC, together with the relevant educational materials (see under 'clinical topics'). The first session, which will last approximately 90 minutes, will address the diagnostic test ordering behaviour of the individual GPs and will have the structure described under 'session structure' (Table 2). During this session, the GPs will discuss their diagnostic test ordering patterns and relate them to the guidelines provided. Individual and group working agreements will be created after barriers to change have been discussed. The second session will have the same structure, but the subject for discussion will be physicians' prescribing performance. This session will end by creating group and individual working agreements about preferred medication. Barriers to change from an individual perspective will again have to be discussed. After this first topic has been completed, the cycle will be repeated, for a new topic, as shown in Table 3. At the start of this new cycle, the group will reflect on the previous agreements, and revise them if necessary. The working agreements will then be prepared for further dissemination in the practices. Each session will be chaired by a member of the LQIC itself. When test ordering is discussed, a local representative from the diagnostic centre will be present, while a local community pharmacist will be present when pharmacotherapy is discussed. They will act as moderators, not as chairpersons.

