### Analysis

Analysis will be based on the intention-to-treat principle. Data on GPs lost to follow-up will be extracted from the various databases if possible.

We will analyse covariance using test and drug volumes during the intervention period as the dependent variables, and the baseline data and the explanatory variables as independent variables. The analysis will be repeated using proportions stemming from prescription performance indicators, if available. The unit of allocation to the trial is the LQIC. In larger practices with more than one GP, not all volumes of tests ordered and drugs prescribed will be traceable to an individual GP. In these cases, the unit of analysis will be the practice as a whole. Because of this unit of analysis error, the data will be analysed using multilevel modelling. Data on drugs and tests will be clustered to individual GPs at level one, the practice at level two, the LQIC at level three and the region at level four.

The nature of this study makes it difficult to blind the participants, except for the tests or drugs serving as controls in the other arm. The data analyst will be blinded for the allocation result. Costs of the intervention will be calculated. A cost-effectiveness analysis will be based on these figures. We will use cost minimization analysis from a societal perspective, assuming that the strategy will reduce redundant testing and prescribing. If there are signs of improvement of care (higher scores on the performance indicators), the impact on health may be estimated by modelling the future gains and benefits. Data include costs of coordinating the strategy by the regional contact group, of preparing feedback reports and of chairing the GP groups. The costs of the entire test ordering strategy by [name] were €554.70 per GP per six months (three meetings). The major part of the cost of this strategy consisted of opportunity costs, *viz *the costs of the GPs' time spent attending the session. Because GPs were already attending these meetings and were financially compensated, it seems fair to ignore the opportunity costs. This results in costs of the test ordering strategy of €92.70. The gains obtained by improving test ordering behaviour were €301.00 per GP per six months. Introducing the test ordering strategy would save €208.30 (92.70 to 301.00) per GP per six months [33]. Because prescribing costs are higher, the cost reductions gained by reducing superfluous prescribing should also be higher.

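### Effect outcome 1 exists only where a group reached a working agreement after randomisation, so it describes agreement-making groups and cannot be presented as the intention-to-treat effect

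*Protocol article*

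**What the plan says.** Under Effect evaluation, outcome 1 covers the volumes of particular tests and drugs "for which the group has agreed that change, either decrease or increase, would be necessary". The matching research question (Effect, question 1) takes the desired direction from the groups' working agreements and compares with baseline.

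Both steps that fix what is measured come after allocation. The Intervention section says "After randomization to arm A or B, each group can choose from the corresponding set of five clinical topics allocated to that arm", and of the sessions, "Individual and group working agreements will be created after barriers to change have been discussed".

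Whether agreements come about is itself measured. The Process evaluation lists "actually creating working agreements, following the LQIC strategy, the number of groups that complete participation", and under Measurements the chair reports after each meeting whether agreements were made. The LQIC meeting structure section lets groups adapt the format. The Sample size section states "Anticipating a dropout of 10%, we would need to recruit 50 groups".

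Outcome 2 is defined differently: "The total volumes of tests ordered and drugs prescribed by the participating GPs for the clinical topics chosen". Outcome 3, inter-physician variation, likewise depends on the topics chosen and not on agreements.

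The Analysis section states "Analysis will be based on the intention-to-treat principle" and adds that data on GPs lost to follow-up will be taken from the databases where possible.

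**The concern.** Whether outcome 1 exists for a group-topic depends on something the group does after randomisation, as part of the intervention. Where no agreement is reached, or the group leaves before choosing a topic, there is nothing to score. The provision for lost GPs does not help: it recovers volumes, but not which items count or which direction is desired.

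The trial asks whether a strategy that worked under academic control still works when handed to the field. Failing to reach agreements is one way in which transfer can fail. Outcome 1 takes those cases out of the effect figure. Question 1 is also a comparison with baseline, so within it no control group offsets the selection. A favourable result could be read as the effect in all randomised groups when it applies only to those that reached an agreement.

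**Working it through.** This is mainly a question of definition, so the provisions are set side by side first.

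| Situation of a group on a topic | Outcome 1 | Outcomes 2 and 3 |
|---|---|---|
| Topic chosen, agreement reached, group continues | defined | defined |
| Topic chosen, agreement reached, group then stops | defined, if volumes can be extracted | defined, if volumes can be extracted |
| Topic chosen, no agreement | undefined | defined |
| Group leaves before choosing topics | undefined | undefined |

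Rows three and four are what outcome 1 loses. Row four is what all three effect outcomes lose.

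**Direction of any bias.** The Hypotheses section expects successful implementation to be positively related to group performance, and counts drawing up agreements as part of performance. The Randomization section calls performance level a known confounder and stratifies on it. If these expectations hold, group-topics without an agreement are those where less change is expected, and leaving them out pushes the result upward. This is the plan's expectation, not an established fact.

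**Size.** The plan gives no figure for the share p of group-topics without an agreement, and none for the change in them. Assume, for illustration only, that they show no change at all:

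- all-groups change = (1 − p) × change among agreement-makers
- overstatement factor = 1/(1 − p)

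Taking 20% as the change among agreement-makers (the example in the Sample size section):

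| Assumed p | All-groups change | Factor |
|---|---|---|
| 10% | 0.9 × 20% = 18% | 1/0.9 = 1.11 |
| 30% | 0.7 × 20% = 14% | 1/0.7 = 1.43 |
| 50% | 0.5 × 20% = 10% | 1/0.5 = 2.0 |

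Any change in the groups without an agreement, in the direction that would have been wanted, brings the factor closer to 1.

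**Dropout.** The 44 groups are the number needed before the allowance for loss: 44/0.9 = 48.9, and the plan recruits 50. With 10% loss, 50 × 0.9 = 45 groups remain, so planned dropout does not take the trial below 44.

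**Denominator over all randomised groups.** 50 groups × 3 topics = 150 group-topics. If the 10% dropout (5 groups) all left before choosing, 5 × 3 = 15 of these would have no outcome 1 value; groups that left later would lose fewer.

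**The case against.** The case on the other side is substantial, and parts of it stand.

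- **Question 1 is conditional by nature.** It asks whether agreements were followed, compared with baseline. The effect against controls is question 2, served by outcomes 2 and 3. A reader might infer that the whole effect evaluation is confined to groups that carried out the strategy. The document does not support that: a group that chose topics without agreeing still counts in outcomes 2 and 3, and a group that agreed and then stopped still has an outcome 1 value.
- **Failed implementation is not hidden.** Agreement-making and completion are reported as process outcomes. This stands, but it does not change what the outcome 1 figure represents.
- **Exclusion is nowhere stated.** True, and a scoring rule could sit in an analysis plan that is not shown. But the outcome definition is fixed here, and read literally it gives no value where there is no agreement. The intention-to-treat sentence does not supply one.
- **The size could be read too strongly.** A reader might take the Background statement, "Currently, approximately 50% of the group meetings reach the desired level of performance described by policymakers", as meaning that half the groups would make no agreement. It concerns existing meetings, before the intervention, judged against a standard that also requires feedback, discussion of barriers and evaluation. The session plan sets aside 15 minutes for agreements, and moderators are trained. Nor is dropout the same as having no agreement. A doubling of the effect is therefore not supported.
- **No agreement may mean no change was needed.** Outcome 1 concerns items where the group judged change necessary, and the Discussion recognises that performance may already be good. Such a group is not an implementation failure. This stands and shapes the fix.

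**Conclusion.** The point holds in a limited form. Outcome 1 and question 1 are defined only where an agreement was reached after randomisation. The before-after result therefore describes group-topics with an agreement, not all randomised groups, and it cannot carry the intention-to-treat label.

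It will tend to overstate the effect of transfer if agreement-making goes with better performance. That rests on the plan's own hypothesis. The amount cannot be computed from the document; the factors of 1.11 to 2.0 depend on assumed shares and on zero change in the remaining groups, which the document does not support.

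Outcomes 2 and 3 are affected only through groups that leave before choosing topics. The consequence is a limit on what outcome 1 can show, not a failure of the trial's controlled comparison.

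**What to change.** 1. Keep the outcome 1 volume analysis, state that it is conditional on an agreement having been reached, and do not present it as the intention-to-treat effect.
2. Add, and do not substitute, the proportion of all group-topics that moved in the agreed direction. The denominator is every randomised LQIC times its three intended topics. Group-topics without an agreement stay in it as not moved. Where the post-meeting forms allow, show those in which the group judged no change necessary separately from those in which the topic was not done or the group dropped out. Where a topic has several agreed items, state beforehand what counts as moved.
3. Rest the conclusion about the strategy's effect on the controlled comparison in question 2 over all randomised groups, with a stated rule for groups that left before choosing topics.

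The cost is a few sentences of analysis wording and a little more analysis work. The forms already record whether an agreement was made; the reason for its absence may not always be recoverable. The headline figure will be less favourable. The added proportion remains a comparison with baseline, because control groups make no agreements on those topics, so it complements question 2 and does not replace it.

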#### Cost evaluation

The costs of implementing the LQIC strategy.

### Explanatory variables

We will monitor data that are known to moderate quality assurance strategies. Therefore the following data will be gathered prior to the intervention: group size, age and gender of GPs, type of practice, number of patients registered with the practice, number of patients a GP is accountable for, number of working hours a week per GP, number of working hours a week for the group practice as a whole, distance to the hospital/diagnostic centre, responsibility for training GP trainees, total number of GPs collaborating in the practice, whether a GP admits sales representatives from pharmaceutical firms and if so how often, involvement in developing national guidelines, and GPs field(s) of special expertise.

All medical coordinators will be asked if problem-based test ordering forms are used in their region and to send us a copy of such a form.

### Measurements

Prior to randomization, the chair of the group will be asked to fill out a short pre-randomization form, with which we will be able to determine the number of GPs in the group and be able to assess the level of group performance [See Additional file 1]. Data on test ordering and prescribing behavior will be extracted from the existing databases at baseline (t = 0) and t = 6 months, t = 12 months and t = 18 months. The dataset obtained at t = 0 and the final set will be used for a before-after analysis. A new questionnaire will be sent to the chair, assessing the level of group performance after the intervention. After each meeting, the chair will be asked to fill out a form with questions about the structure of the session, whether working agreements were created, whether barriers to change were discussed and if so what the nature of these barriers was, what educational materials were used, and the group members' experiences with the strategy.

The process of implementing the strategy in the south of the Netherlands will be monitored. Participants will be questioned about their experiences with the strategy. Participating GPs will be asked to report their experiences with the strategy, and to provide us with the necessary details on the sessions they have attended. After each session, the targets set by each group will be recorded.

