**Methods:**

In order to evaluate the effects, costs and feasibility of this new strategy we plan a multi-centre cluster randomized controlled trial (RCT) with a balanced incomplete block design. Local GP groups in the south of the Netherlands already taking part in pharmacotherapeutic audit meeting groups, will be recruited by regional health officers. Approximately 50 groups of GPs will be randomly allocated to two arms. These GPs will be offered two different balanced sets of clinical topics. Each GP within a group will receive comparative feedback on test ordering and prescribing performance. The feedback will be discussed in the group and working agreements will be created after discussion of the guidelines and barriers to change. The data for the feedback will be collected from existing and newly formed databases, both at baseline and after one year.

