##### Effect

1. Do the volumes of tests ordered and drugs prescribed change in the preferred direction, as described in the working agreements of the LQICs, compared to baseline?

2. What is the effect of this strategy on GPs' test ordering and prescribing behaviour in terms of interphysician variation and total volumes of tests and prescriptions with respect to specific clinical topics, compared to that among GPs exposed to the same strategy but for other topics?

3. Is any gain in the level of group performance predictive of the effect achieved?

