### Extraction of feedback data

Data on test ordering behaviour will be extracted by the regional coordinators from the various databases available at the participating hospital laboratories or primary care diagnostic centres. Each centre will receive a data fact sheet prescribing the required data format. This format is based on rational criteria for laboratory test registration to facilitate the integration of the individual databases into one main database. All datasets on diagnostics will be combined into one newly formed database, to be maintained by UM (Figure 2). Data on prescribing behaviour will be extracted from the databases of health insurers and collected into one database, as has already been done at our institute. This database consists of the reimbursements for prescriptions written by GPs for approximately 5.5 million persons in the south of the Netherlands. Feedback will then be derived from the two main databases and processed into graphical comparative feedback reports. Data will be presented as the volume of tests ordered (*e.g*., haemoglobin) or defined daily dosages (DDDs) prescribed per 1000 patients per six months. Participating GPs will receive their data as clustered column charts, each cluster presenting the data for the individual GP, the practice in which he or she works, the small group and the wider region. An example of such a graphical feedback report is shown in Figure 3.

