### Time schedule

The intervention period will start in September 2007 and run through the spring of 2009. Process evaluation will start when all groups are included. During the intervention, new datasets will be obtained every six months in order to keep the databases up-to-date for future use in new sessions.

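### On the natural reading, the before-after analysis for effect question 1 compares opposite half-years, so season can pass for change; the analysis windows should be stated and season-matched

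*Protocol article*

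**What the plan says.** Measurements lists the extractions as "at baseline (t = 0) and t = 6 months, t = 12 months and t = 18 months" and then says: "The dataset obtained at t = 0 and the final set will be used for a before-after analysis". The last time point listed is 18 months.

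Three other places bear on what those datasets cover:

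- Extraction of feedback data expresses test counts and drug volumes per six months; for drugs the unit is "defined daily dosages (DDDs) prescribed per 1000 patients per six months". This unit is given for the feedback reports.
- Time schedule says that "new datasets will be obtained every six months", and gives the calendar: "The intervention period will start in September 2007 and run through the spring of 2009".
- The Methods paragraph of the abstract has the feedback data collected "both at baseline and after one year".

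Effect question 1 asks: "Do the volumes of tests ordered and drugs prescribed change in the preferred direction", as set out in each group's working agreements and relative to baseline. It names no control arm. Effect question 2 compares with GPs who receive the strategy for other topics. The Analysis section plans an analysis of covariance of volumes during the intervention period, adjusted for baseline. Season is not mentioned anywhere.

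**The concern.** A before-after comparison without a control attributes every difference between the two windows to the intervention. If one window holds the summer holiday months and the other the winter months, a seasonal pattern in consultations, tests or prescriptions becomes part of the estimated change.

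The direction of the error depends on the target. If volumes are lower in summer and the baseline is the summer half, a volume that a group agreed to reduce will look as if it fell too little or even rose. A volume that a group agreed to increase will look as if it improved. With the opposite seasonal pattern the errors reverse. Effect question 1 pools targets in both directions, so a shared seasonal shift would count as success for some working agreements and failure for others.

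**Working it through.** **1. Calendar.** September 2007 (Time schedule) plus 18 months (Measurements) is March 2009. This agrees with the stated end in spring 2009, so the 18-month extraction is consistent with being the final set.

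**2. Windows.** Assume that each extraction covers the preceding six months and that t = 0 is about 1 September 2007.

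| Set | Period covered |
|---|---|
| t = 0 | March-August 2007 |
| t = 12 months | March-August 2008 |
| t = 18 months | September 2008-February 2009 |

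A lag of 18 months is one year plus six months. Six-month windows at that lag therefore fall in opposite half-years whatever the start month. At a lag of 12 months they fall in the same half-year.

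**3. Size under a summer dip (assumed).** Let July and August run a fraction d below the other months, with no change in practice. The mean of the March-August window, relative to September-February, is 1 - (2/6)d. The apparent change is 1/(1 - d/3) - 1. A true fall of 10% is seen as 0.90/(1 - d/3) - 1.

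| d | Baseline window | Apparent change, no true change | True 10% fall seen as |
|---|---|---|---|
| 0 | 1.00 | 0.0% | -10.0% |
| 0.15 | 0.95 | +5.3% | -5.3% |
| 0.30 | 0.90 | +11.1% | 0.0% |

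**4. Size under a smooth yearly cycle (assumed).** Take monthly volume as 1 + a·cos(2π(m - peak)/12) and average it over each six-month window. The apparent change is the ratio of the two window means minus 1.

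| Amplitude a | Peak in mid-January | Range over all peak dates |
|---|---|---|
| 5% | +4.6% | -6.2% to +6.6% |
| 10% | +9.4% | -12.0% to +13.6% |

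As a check on the worst case at a = 10%: a half-year mean is 1 ± 0.10 × 2/π = 1 ± 0.0637, and 1.0637/0.9363 - 1 = 13.6%.

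**5. Benchmark.** The Background reports a fall of 8% to 12% in test volumes over six months in the earlier trial of the test-ordering strategy. The Hypotheses section expects similar changes here.

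**6. After a change of windows.** In the same cosine model, a 12- or 24-month lag between six-month windows, or 12-month windows at both ends, gives a seasonal shift of 0.0% at every amplitude tried (5% to 20%).

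**7. Between arms.** Both arms are measured in the same calendar windows. A seasonal factor common to both multiplies both and cancels from their ratio.

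**The case against.** The strongest reply is that the six-month analysis window is inferred. The per-six-months unit describes how feedback is presented, the six-monthly refresh serves new feedback sessions, and Measurements gives extraction times without look-back lengths. With 12-month windows the problem disappears, and an article may leave such detail to a fuller document. This stands, and it makes the point conditional. It does not remove the point: six months is the only period the article attaches to these volumes.

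Second, the abstract's one-year follow-up would put both windows in the same season. That is correct, but Measurements is the more specific text and agrees with the calendar in Time schedule. The two statements conflict and have to be reconciled.

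Third, the seasonal figures are assumptions. This also stands. Drugs taken long term, such as statins, metformin or levothyroxine, may vary little over the year, and for them the shift may be close to zero. The sample-size section works with a larger change, from 35% to 55%, but it presents this as an illustrative target; the expectation in Hypotheses is the effect of the earlier trial.

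A reader might also infer more than the document supports:

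- **That the randomised comparison is biased.** It is not, for any seasonal pattern common to both arms.
- **That the analysis of covariance loses precision through an out-of-season baseline.** Nothing in the article shows this. A shift shared by all GPs leaves the correlation between baseline and outcome unchanged, and the dependent variable is not tied to one half-year.
- **That the mismatch persists however the outcome window is defined.** Using the 12-month set, or 12-month windows, removes it.

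**Conclusion.** The point holds in a limited, conditional form. If the datasets cover six months each and the final set is the 18-month one, the uncontrolled before-after analysis for effect question 1 compares opposite half-years and cannot separate season from change in behaviour.

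The size cannot be fixed from the document. Under the assumed summer dips it runs from 0% for non-seasonal items to 5.3% to 11.1%. The upper part of that range is as large as the expected 8% to 12%, so a real fall could be hidden or an apparent one produced. How far this applies will differ by topic.

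Effect question 2 is not affected by shared seasonality. The point is therefore a cheap improvement to a secondary contrast and no threat to the trial's main comparison. Confidence is medium, because the window length is inferred and the abstract points to a different follow-up time.

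**What to change.** First, reconcile the follow-up time in the abstract with that in Measurements, and state which calendar months form the baseline and final windows. Then choose one of these for effect question 1:

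1. **Compare t = 0 with the 12-month set.** This needs no extra data. The cost is that the last half-year of the intervention period drops out of this contrast.
2. **Use 12-month windows at both ends**: the year before t = 0, and the 12- and 18-month sets together. This needs six more months of baseline history.
3. **Keep the 18-month set** and take as its baseline the same half-year before t = 0 (about September 2006-February 2007). This also needs the earlier history, and the baseline lies further back.
4. **Answer the question against the concurrent arm**, using the other arm's volumes for the same tests and drugs over the same months. This needs no extra extraction.

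Options 2 and 3 draw on databases that already exist, but the Discussion warns that extraction is a burden for the diagnostic centres, so the longer pull has a small real cost. Options 1 and 4 avoid it. In each case the text change is a sentence or two in Measurements or Analysis.
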